**Methods/design:**

We describe an ongoing parallel, two-armed, non-inferiority randomised controlled trial that compares routine and teledental pathway of dental care in children aged 4–15 years (*n* = 250). Participating schools in Western Australia will be randomly assigned to the control or teledental group, approximately three schools in each group with a maximum of 45 children in each school. All participants will first receive a standard dental examination to identify those who require urgent referrals and then their teeth will be photographed using a smartphone camera. At the baseline, children in the control group will receive screening results and advice on the pathway of dental care based on the visual dental screening while children in the teledental group will receive screening results based on the assessment of dental images. At 9 months follow-up, all participants will undergo a final visual dental screening. The primary outcomes include decay experience and proportion of children become caries active. The secondary outcomes include the diagnostic performance of photographic dental assessment and costs comparison of two pathways of dental care.

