### Participants’ recruitment

We will approach approximately 25 schools in WA, initially by email with a telephone follow-up, complying with good practice and research governance for undertaking studies within the education system. Parents of children aged 4–15 years, attending selected schools, will be invited to allow their children to take part in research using several advertising strategies including, schools’ newsletters, email lists and notice boards to help in achieving target sample. The inclusion criteria include children, aged 4–15 years, who are attending schools or college in WA in which the school principal has permitted for their school to be included in the trial will be included in the study, subject to their parents giving written consent. The exclusion criteria include children of the same age, in the same schools for whom parents have not given written permission for their children to take part. Once written permission is obtained from the schools, an information sheet and consent form will be mailed to parents of school children attending participating schools to invite them to participate. Besides, an information session will be scheduled for parents to provide more information about the project and respond to their enquiries.

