### Allocation

To avoid spill-over effects within a school, we will conduct randomisation using the school as the unit of allocation because the intervention is implemented at the level of the school (Fig. 3). The schools will be randomly allocated in a 1:1 ratio to one of the teledental or control group. For allocation of the participants, a computer-generated list of random numbers will be used. To approximate equality of sample sizes in the study groups, we will use block randomisation with computer-generated randomly permuted blocks of 4 at each school. School-specific randomisation lists are concealed by an independent researcher, and kept in sequence and opened as participants are examined at the baseline and found eligible for enrolment. The research team and data analysts will be blinded to group allocation and will not be aware of the randomisation procedure. Study participants (and their parents/guardians) and OHTs providing the intervention and/or collecting data cannot be blinded to group allocation.

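### Opening the list child by child at the baseline examination cannot conceal a whole-school allocation, and the eligibility check placed there has no stated criterion

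*Protocol article*

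**What the plan says.** All references are to the protocol article.

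- **Unit of allocation (Allocation).** "we will conduct randomisation using the school as the unit of allocation because the intervention is implemented at the level of the school", and "The schools will be randomly allocated in a 1:1 ratio to one of the teledental or control group". The reason given is avoidance of spill-over within a school.
- **Sequence (Allocation).** The section then turns to allocating participants: "we will use block randomisation with computer-generated randomly permuted blocks of 4 at each school".
- **When lists are opened (Allocation).** An independent researcher conceals school-specific lists, which are "kept in sequence and opened as participants are examined at the baseline and found eligible for enrolment".
- **Eligibility (Participants' recruitment).** "The inclusion criteria include children, aged 4–15 years, who are attending schools or college in WA in which the school principal has permitted" the school's inclusion, subject to written parental consent. The only exclusion is absence of that consent.
- **Consent (Participants' recruitment).** "Once written permission is obtained from the schools, an information sheet and consent form will be mailed to parents of school children".
- **Purpose of the examination (Abstract, Methods/design).** "All participants will first receive a standard dental examination to identify those who require urgent referrals".
- **Blinding.** Allocation says "Study participants (and their parents/guardians) and OHTs providing the intervention and/or collecting data cannot be blinded to group allocation", while the research team and analysts are to be blinded. The Visual dental examination section says that the OHTs who carry out the baseline screening do not know which arm the school is in.

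**The concern.** The text places an eligibility decision at the examination, but no eligibility criterion needs the examination. Whoever makes that decision has no written rule to apply, and makes it just when the child's caries status becomes visible.

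That would matter little if each opening revealed one child's assignment. With whole-school allocation it reveals the assignment of every child still to be seen in that school. Concealing a list and opening it in sequence protects individual randomisation. It does not protect a cluster allocation after the first child.

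What is at stake is comparability of the arms in caries at entry. Both primary outcomes concern caries, and there are about three schools per arm, so chance will not reliably even out differential entry. The covariates named in Data analysis are survey items (brushing, dental visits, age, Indigenous status, area index, insurance, parental education). Baseline DFT/dft is not among them.

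**Working it through.** **1. Does any eligibility criterion depend on the examination?**

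| Criterion (Participants' recruitment) | Can be settled before the examination? |
|---|---|
| Age 4–15 years | Yes, from school or parent records |
| Attends a school whose principal has agreed | Yes |
| Written parental consent | Yes, on paper |
| Exclusion: no written consent | Yes, on paper |

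None does. The Abstract describes those examined as participants already and gives urgent referral, not entry, as the purpose of the examination. The step of being found eligible at the examination therefore has no content in the article.

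**2. How many children are entered after their school's arm can be known?**

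Inputs: three schools per group, so 6 schools (Sample size calculation); 250 children in total (Abstract); at most 45 children per school (Sample size calculation).

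With one arm per school, only the first child opened in each school is entered before disclosure:

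- Planned total: (250 − 6) / 250 = 244/250 = 97.6%.
- At the maximum per school: 6 × 45 = 270, and (270 − 6) / 270 = 264/270 = 97.8%.

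These are upper limits. They count children whose arm can be known, and do not say that the person entering them knew it.

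**3. The other reading: individual allocation in blocks of 4.**

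Opening the next entry after eligibility is confirmed is then ordinary concealment, and the disclosure in step 2 does not arise. A smaller weakness remains if the block size is known. There are 6 possible sequences of two and two. In 2 of them the last two places are certain, and in the other 4 only the last place is. That gives 2×2 + 4×1 = 8 of 24 places, or one third. This reading contradicts the stated unit of allocation and its spill-over rationale.

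**4. Illustration of what selective entry would do.**

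Input from the plan: caries prevalence 35% (Sample size calculation). Assumption: a fraction f of children with caries fails to enter in one arm only. Prevalence in that arm = 0.35(1 − f) / [0.35(1 − f) + 0.65].

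| f (assumed) | Calculation | Prevalence | Gap from 35% |
|---|---|---|---|
| 0.10 | 0.315 / 0.965 | 32.6% | 2.4 points |
| 0.20 | 0.280 / 0.930 | 30.1% | 4.9 points |
| 0.30 | 0.245 / 0.895 | 27.4% | 7.6 points |

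**5. Sample size.** The plan's 125 per group reproduces: 1.96² × 0.90 × 0.10 / 0.10² = 34.6, rounded up to 35; 35/0.35 = 100, that is 35 with and 65 without caries; 100/0.8 = 125. Nothing in this point changes it.

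**The case against.** The strongest reply has four parts.

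**Examiner blinding.** The Visual dental examination section says that the screening OHTs are blinded to the school's arm, and an independent researcher holds the lists. If both held throughout, an examiner could not select by arm. But Allocation says that data-collecting OHTs cannot be blinded. The two statements conflict, so the safeguard can be neither relied on nor dismissed.

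**Child-level wording.** The sentence on opening lists follows text about allocating participants in blocks of 4, where opening after eligibility is good practice. This stands as a fair reading of that sentence alone. It cannot be squared with the school as unit of allocation, so the section needs correcting on either reading.

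**No exclusion on findings is stated.** A reader might infer that urgent or severe cases would be dropped at the examination. The article does not support that: it refers such children and calls them participants. Being found eligible may mean no more than checking age and consent on the day.

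**Consent timing.** A reader might also infer that parents consent with the arm known. Forms are mailed after the school gives permission, and lists are opened at the examination, so consent for the first children seen should come before opening. The article does not say when a school's arm is disclosed relative to consent, and the flow diagram is not available here. Silence in a condensed article is weak evidence, and only late consents in a school already opened would be exposed.

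It is also right that a gap in baseline prevalence would not pass directly into the outcomes. DFT/dft is measured at both visits, and the second primary outcome counts new caries in teeth that were caries-free at baseline.

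**Conclusion.** The point holds as a defect in the stated procedure. On the article's own unit of allocation, child-by-child opening conceals the arm for only the first child in each school, leaving up to 97.6% of the planned 250 children to be entered after disclosure. It does so at an eligibility step for which no criterion is given.

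This rests on taking the school as the unit of allocation, which the article states first and justifies. It shows an open route to selective entry, not that selection has occurred or is likely. The gap of 2.4 to 7.6 points in baseline prevalence illustrates assumed losses confined to one arm and is not an estimate. The correction is worth making because it is cheap and closes the route whichever blinding statement proves right.

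**What to change.** In Allocation, replace the wording on opening lists at the examination with three statements:

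1. A child is enrolled once age, school and written consent are confirmed.
2. No consented child is excluded from the trial or its analyses because of examination findings. Referral is not affected.
3. Each school's list of consented children is lodged with the independent researcher before that school's allocation is disclosed.

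In the same revision, reconcile the blocks of 4 at each school with whole-school allocation, and reconcile the two statements on OHT blinding (Allocation; Visual dental examination).

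The cost is a change of wording and of the order of steps. Consents that arrive after a list is lodged are not added, which may lose a few children.

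Study status says that data are already being collected, so some schools may be past this point. For those schools, report by arm any consents or exclusions made after disclosure, and run a sensitivity analysis without the late entrants.

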#### Visual dental examination

A standard dental screening (without radiography) will be performed by registered OHTs (operators) who are blinded to the group allocation of the school. Head-mounted lighting, disposable mirrors and probes will be used to conduct the visual dental screening. Findings from the visual dental assessment will be recorded on an oral health assessment form that follows the guidelines for oral health surveys developed by the WHO [35]. Following the completion of the baseline dental screening, parents of school children allocated to the control group will receive a copy of the screening results based on the visual inspection performed by onsite OHTs. Based on the severity and urgency of dental conditions, children with active caries will be referred to local dental providers for further investigations. Children who are screened caries-free or at low-risk, will not receive active treatment other than OHP leaflets.

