#### Photographic dental assessment

As per dental screening protocol used in previous trials [26, 27], tele-assistants (trained research assistants) will acquire still dental images from children using a novel image acquisition App installed in smartphone devices (Fig. 1). The tele-assistants will be provided with a dental photography protocol and will receive hands-on training on how to use the image acquisition App and capture good images. Disposable cheek retractors will be used to assist in viewing teeth during dental photography. Using the mobile App, the tele-assistants will first create a basic registration (includes a unique ID, age in years, gender and school name) for each participant. Then a minimum of five still dental images per child will be taken (front, right lateral, left lateral, upper occlusal, and lower occlusal views). Following the completion of dental photography and creating a record on the App, each participant’s set of data (including dental images and anonymous patient details) will be then directly uploaded from the mobile App to a secure drive located at the CSIRO, for later evaluation by charters (Fig. 4). The assessment of dental images will be performed independently by 2–4 registered OHTs (charters). Charters will receive instructions on how to log in and use the web-based application (Remote-I), review images and insert findings back to the system. After selecting a record from the database, a list of dental images and a predefined assessment chart appears for the charter to insert their findings. The chart includes a digital oral health assessment form, which aligns with the WHO protocol for oral health assessments [35]. The system enables charters to independently review dental images and submit reports or treatment plans to the Remote-I system (Fig. 2). The assessment of dental caries will be completed at the tooth level rather than the tooth surface, based on a protocol developed by the WHO [35]. A copy of the screening results will be mailed to the parents of children in the teledental group that includes advice on the pathway of dental care or OHP material based on the assessment of dental images .

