### Outcome assessment

*Primary outcomes* include decay experience in either dentition as measured by the DFT/dft (decay, filled teeth) index at the baseline and 9-month follow up. Teeth will be classified as carious if have arrested caries, caries into dentine or enamel level caries. In addition to the proportion of children becomes caries-active at the 9-month follow-up which refers to the percentage of children developing one or more new caries in any of the previously caries-free teeth when assessed at the baseline. Data will be collected from one of our system’s functional components running on the backend to automatically record dental assessments based on dental images and through the oral health assessment forms completed by OHTs in the control group.

*Secondary outcomes* include the diagnostic performance of photographic dental assessment versus standard dental examination at the baseline. The participants’ dental care utilisation patterns collected via a baseline survey (Additional file 2) and adapted from Kopycka-Kedzierawski et al. [36]. Also, costs comparison between the two pathways of dental care will be conducted to identify the least costly alternative. The resources for the usual pathway of dental care will include vehicle costs, admin costs (e.g. telephone appointments, printing services and postage) and costs of consumables used in visual dental screening and the dental practitioner’s time. The resources for the teledental pathway of dental care include: software licence fees, ICT equipment, Internet and software engineer’s time, admin costs (e.g. telephone appointments, printing services and postage), costs of consumables used in dental photography, tele-assistants (photographer) time, and offsite dental practitioners’ time for reviewing dental images. Dental care costs for all children include the following: restorations, restorations with crowns and extractions. The costing data will be based on those incurred by the health system and will be derived from a survey and web-based open-access sources [37].

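### The unqualified claim that the research team and analysts are blinded cannot cover costing or report preparation, and it clashes with the stated source of the outcome data

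*Protocol article*

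**What the plan says.** All references are to the protocol article.

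- **Blinding claim (Allocation):** "The research team and data analysts will be blinded to group allocation and will not be aware of the randomisation procedure". The next sentence lists those who are not blinded: the children, their parents or guardians, and the therapists ("OHTs providing the intervention and/or collecting data cannot be blinded to group allocation"). Nobody who handles costs, screening reports or analysis is exempted.
- **Source of outcome data (Outcome assessment):** directly after the primary outcomes are defined, data are said to come from the automatic records of the image system and "through the oral health assessment forms completed by OHTs in the control group".
- **Costs (Outcome assessment, Data analysis):** the two pathways have separate resource lists. The usual pathway has vehicle costs, visual-screening consumables and practitioner time. For the other arm, "The resources for the teledental pathway of dental care include: software licence fees, ICT equipment" opens a list that goes on to Internet, engineer, tele-assistant and offsite review time. The cost minimisation includes the initial screening.
- **Reports to parents (Visual dental examination, Photographic dental assessment):** control families receive results based on the visual inspection. For the other arm, "A copy of the screening results will be mailed to the parents of children in the teledental group", and these are based on the images.
- **What every child receives (abstract, Methods/design):** "All participants will first receive a standard dental examination to identify those who require urgent referrals and then their teeth will be photographed". The abstract and Follow up then give all participants the same visual check at 9 months.

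**The concern.** A blinding statement is a property that the trial report will repeat. Here it is made for a whole team and for all analysts, while other sections give some of those people tasks that cannot be done without knowing the arm. The objectives carry a favoured direction for both efficacy (teledental as effective as routine care) and cost (teledental cost-saving), so knowledge of the arm during analysis is not a neutral matter. If the sentence is carried unchanged into the results paper, part of the analysis will be described as protected when it was not. For the primary outcomes, readers will not be able to tell which of two conflicting data flows was used.

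**Working it through.** No formula applies. The check sets the sections side by side and asks, for each task, whether it can be done without knowing the arm.

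1. **Assigning screening costs.** Inputs: the two resource lists under Outcome assessment, and the inclusion of initial screening in the cost comparison under Data analysis. Software licences and tele-assistant time can be charged only to the group known to be teledental, and the usual-pathway screening items only to the other. Labelling the arms A and B does not help, because the costs themselves must be attached to the correct pathway. The claim fails here by construction.

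2. **Treatment costs.** Restorations, restorations with crowns and extractions are one list for all children. These lines do not identify the arm.

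3. **Preparing the reports.** The basis of the report is the visual inspection in one arm and the images in the other, so whoever prepares it must know the arm. The article does not name that person. The claim therefore fails for that role if it lies within the research team, but this says nothing about analysts.

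4. **Analysing DFT/dft and caries-active status.** There are two readings.
   - *Outcome assessment, read literally:* image-system records on one side and forms from control-group therapists on the other. The source of a record would then show its arm, contrary to Allocation.
   - *Abstract and Follow up:* every child has a visual examination and photographs at baseline, and a visual check at 9 months. A visual form then exists for every child examined, in either arm, and the source reveals nothing.

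   The two readings cannot both describe the data flow. Only the second is compatible with a blinded efficacy analysis.

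5. **School identity.** The image registration "includes a unique ID, age in years, gender and school name". All children are photographed, so a school name appears in both arms and does not disclose the arm by itself. It does so only if allocation is by school and the reader also has the link from school to arm. Allocation names the school as the unit, but also describes permuted blocks of 4 within each school, under which school would not determine arm. Data management promises that identifiers are replaced by a code, without mentioning arm labels.

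**The case against.** The strongest reply is that the primary analysis can be blinded under the protocol's own procedures. Both baseline methods are applied to everyone, the 9-month examination is common, an independent researcher holds the lists, and the clause about the control group may be loose drafting. The cost comparison is a secondary outcome, and its analyst need not be the efficacy analyst. Coded labels and the timing of code-breaking normally sit in an analysis plan or data-management plan, which is not shown. All of this stands, and it limits the point. It does not rescue the sentence under Allocation, which makes no distinction between analyses, or the sentence under Outcome assessment, which states a different data flow.

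Several stronger readings are tempting, and the documents do not support them:

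- *Every outcome record discloses the arm.* This follows only from the literal data-source sentence, which the abstract and Follow up contradict.
- *Every cost line discloses the arm.* Treatment costs use one list for all children.
- *With about three schools per group, learning the arm of six schools unblinds all 250 children.* This assumes allocation purely by school and access to the school-to-arm link.
- *Analyst blinding is the only safeguard.* The article also prespecifies the model family, the covariates and the efficacy measure, and the trial is registered.

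**Conclusion.** The concern holds in a limited form. The blanket statement cannot be true for the person who assigns pathway-specific screening costs, nor for the person who prepares the arm-dependent reports if that person belongs to the research team. It also conflicts with the data-source sentence under Outcome assessment, which is in turn inconsistent with the abstract and Follow up. The documents do not show that the analyst of the primary outcomes will be unblinded. The effect on bias cannot be computed from them and is probably modest. What needs correcting is a stated property that the design does not have in full.

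This conclusion concerns analysts and the research team. Separately, Allocation says therapists collecting data cannot be blinded, while Visual dental examination describes screening "performed by registered OHTs (operators) who are blinded to the group allocation of the school". Those two statements must also be reconciled.

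**What to change.** 1. **Outcome assessment:** state that DFT/dft and caries-active status come from the visual examination forms in both arms, at baseline and at 9 months. Use image-system data only for diagnostic performance and for the teledental reports.
2. **Efficacy file:** have the independent researcher who already holds the lists prepare it, with coded arms and coded schools.
3. **Allocation:** restrict the blinding claim to the efficacy analysis run on that file.
4. **Allocation, same paragraph:** state that the staff who do the costing and prepare the reports are not blinded. If one person does both the efficacy analysis and the costing, say so and state the order of the two.

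The cost is a few sentences, one coded extract and a narrower blinding claim. Recruitment, sample size and trial procedures do not change.
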